**Care close to home**		
1	Proportion of patients referred to the Perinatal Center of the University Hospital	SHI routine data of the participating health insurance company
	Proportion of patients who gave birth in a defined facility level	project database, SHI routine data of the participating health insurance company
	Proportion of patients and mean number of virtual feto-neonatal board meetings	project database
	Frequency of disciplines involved in virtual feto-neonatal board meetings	project database
	Proportion of patients with psychosocial consultation within two weeks after diagnosis or directly at patient contact	project database
	Proportion of patients who make use of further offers of help	project database
	Maternal risks and complications during inpatient stay measured by ICD and OPS codes	SHI routine data of the participating health insurance company
2	Number of postnatal transports	project database
	Proportion of transferred newborns	project database
	On transport: time of neonatologist at participating hospital	project database
	Condition of newborn during transport measured by body temperature and blood glucose in each case in participating hospital and Perinatal Center of the University Hospital	project database
	Time (in minutes) until a neonatologist is present in the delivery room postnatally (also virtually, if necessary)	project database
	Proportion of infants with hypoglycemia in the first 24 h	project database
	Number of teleconsultations in the delivery room	project database
	Proportion of newborns with teleconsultation in case of deterioration of condition on ward	project database
	Number of deceased newborns	project database, SHI routine data of the participating health insurance company
3	Proportion of newborns with antibiotic therapy	project database
	Average duration of antibiotic therapy	project database
	Proportion of newborns whose therapy was terminated after 36–72 h	project database
	Proportion of newborns with pathogen-specific adjustment of therapy after pathogen identification	project database
	Proportion of newborns with use of reserve antibiotics	project database
	Proportion of reserve antibiotics in total antibiotic consumption	project database
	Proportion of newborns with adequately performed pharmacologic surveillance	project database
4	Length of stay of newborns at the Perinatal Center of the University Hospital originating from the participating hospitals	project database, SHI routine data of the participating health insurance company
	Total duration of inpatient care of newborns from participating hospitals	project database, SHI routine data of the participating health insurance company
	Proportion of newborns who had to be transferred back to the Perinatal Center of the University Hospital after transfer to participating hospital	project database, SHI routine data of the participating health insurance company
5	Proportion of patients for whom the previously individually assessed need for follow-up care and networking was achieved	project database
	Proportion of guardians with offers of help (conversations/guidance by staff of the clinic providing care, consultations with psychiatry or psychosomatics of the clinic providing care, referral to other offers of help (e.g. youth welfare office, family midwife, home help, etc.) by clinic providing care, help refused, no need for help seen on the part of the clinic providing care)	project database
	Proportion of guardians who used IB#5 measures	project database

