Primary hypothesis: The intervention bundles (IB) of the HCNSB improve care close to home compared to current routine care.

Secondary hypotheses:

The IB increase job satisfaction and the feeling of safety of health professionals caring for premature and sick newborns. IB furthermore increase patients’ and families’ satisfaction with care, resilience and quality of life and reduce depressive, anxiety and stress symptoms.The IB are cost-effective from a statutory health insurance (SHI) perspective.

Qualitative research questions:

Which barriers hinder health professionals, pregnant women and families of newborns to use the IB?How do the IB influence the satisfaction and sense of safety of health professionals? How do they influence the patients’ sense of safety?

A cluster-randomized controlled stepped-wedge design (SW-cRCT) was chosen to investigate the hypotheses and research questions. Randomization will be performed at the hospital respectively outpatient office level.

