### Eligibility criteria

All patients or newborns meeting the following criteria will be included:

IB#1: Pregnant women with a disorder affecting fetal health (e.g. gestational diabetes) or with a suspicion of a serious disease of the fetus who are cared for on an outpatient basis by a participating prenatal obstetrician,IB#2: Newborns cared for in the delivery room or admitted as inpatients who required resuscitation or intensive care at the participating hospital,IB#3: Newborns admitted as inpatients who receive antibiotic therapy at the participating hospital and/or have a positive microbiologic screening result,IB#4: Premature or sick newborn receiving inpatient care at a participating hospital or the PC-UKD with a suspected need for transfer to the PC-UKD or indication for transfer back close to home,IB#5: Families of newborns hospitalized at a participating hospital for more than 5 days.

The secondary study population consists of outpatient obstetricians and health professionals at the hospitals using IB.

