#### Intervention bundle #2: Neonatal resuscitation

Neonatal resuscitation is a rare event. However, immediate and adequate care of infants is a prerequisite to prevent long-term harm. Specialized neonatal expertise is not available at all facilities, and it can take up to an hour for a neonatal expert from a NICU to arrive on scene. For this reason, it is important that on-site pediatricians have the immediate ability to access the neonatal experts’ support via telemedicine. In some cases, this may even eliminate the need for a neonatologist to travel to the hospital or to transfer the newborn [3].

IB#2 is specifically designed to ensure **immediate availability of neonatal expertise** during neonatal resuscitation. The participating hospital receives **telemedical support** from the neonatology department of the PC-UKD directly after the call. If needed, a neonatal transport can be arranged in parallel and the neonatologist on route can stay informed about the current status of the resuscitation via push messages. In the follow-up of the supported resuscitation, a structured debriefing takes place to optimize the cooperation and to enable quality assurance of IB#2.

The goal is to **reduce neonatal transports** and **improve neonatal care** in critical situations.

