#### Intervention bundle #4: Inter-facility transfer of premature and sick newborns

Once the child is stable and no longer needs the highly specialized neonatal care, it is the aim to transfer them close to home. However, this requires a continuous trans-institutional care and that the parents are appropriately prepared [4].

IB#4 provides support to participating hospitals via neonatal tele-consultations and as part of remote neonatal jour fixes. Through the regular exchange of information about neonates who are eligible for transfer close to home, **transfers from the PC-UKD to the hospitals will be promoted and transfers to the PC-UKD will be reduced**. The transfer process to the participating hospitals is accompanied by psycho-social support services and the parents are involved in these joint “remote rounds” in order to reduce uncertainties and enable an optimal flow of information. The jour fixes also serve as quality assurance measure by debriefing children who have already been transferred.

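### The IB#2 outcome on newborn condition during transport exists only for transported newborns, a group the network aims to shrink, so comparing it by phase risks selection bias

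*Protocol article*

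**What the plan says.** Table 1 of the protocol article, under the heading on care close to home, lists for IB#2: "Condition of newborn during transport measured by body temperature and blood glucose in each case in participating hospital and Perinatal Center of the University Hospital". The same block lists the number of postnatal transports, "Proportion of transferred newborns" and "Proportion of infants with hypoglycemia in the first 24 h".

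The IB#2 population in Eligibility criteria is wider than the transported newborns: "Newborns cared for in the delivery room or admitted as inpatients who required resuscitation or intensive care at the participating hospital".

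The section on IB#2 gives as a goal to "reduce neonatal transports" and says of telemedical support: "In some cases, this may even eliminate the need for a neonatologist to travel to the hospital or to transfer the newborn". The section on IB#4 adds that "transfers from the PC-UKD to the hospitals will be promoted and transfers to the PC-UKD will be reduced".

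Under Assignment of interventions, a newborn's group follows from the phase of the recruiting facility at inclusion, and there is no blinding. The primary hypothesis in Background is: "The intervention bundles (IB) of the HCNSB improve care close to home compared to current routine care".

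**The concern.** The outcome is defined only after an event, transport to the perinatal center, that happens after assignment and that the intervention is built to make rarer. If the network succeeds, fewer newborns in the intervention phase have the outcome at all, and those who do may differ in severity from those transported in the control phase.

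A phase difference in transport temperature or glucose could then reflect who was transported rather than how well newborns were stabilized. If the milder newborns stay local, the remaining transports are sicker and the network looks worse because it worked. If the sickest are kept local, it looks better. No model can supply perinatal-center readings for newborns who never went there.

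At stake is the reading of one secondary row. The primary outcomes, the sample size and the Holm-corrected tests are not affected.

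**Working it through.** **Structure.** The argument has four links, each from the article.

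1. Two-site readings require a transport (Table 1).
2. The IB#2 population includes newborns who are not transported (Eligibility criteria).
3. Group is fixed at inclusion, before any transport decision (Assignment of interventions).
4. Fewer transports to the perinatal center is an aim of IB#2 and IB#4 (sections on these bundles).

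A comparison by phase therefore conditions on a post-assignment event that the intervention is meant to change.

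**Size.** The plan states no figure to reproduce, and every input below is an assumption.

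- Transport tendency T and reading Y (higher = worse) are standard normal with correlation ρ.
- The intervention has no effect on any newborn's Y.
- A proportion p is transported, namely those with T > z, where z is the upper-p normal quantile.
- A reading is out of range if Y > c, with c set so that 20% of all IB#2 newborns are out of range.

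The mean of Y among the transported is ρ·φ(z)/p, and the share out of range is P(Y > c, T > z)/p. The factor φ(z)/p is 0.644 at p = 0.60, 0.798 at 0.50, 0.966 at 0.40 and 1.159 at 0.30.

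For a fall from 60% to 40%, the spurious mean difference is ρ × (0.966 − 0.644) = 0.322ρ. That is 0.032 SD at ρ = 0.1, 0.097 SD at 0.3 and 0.161 SD at 0.5.

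Spurious difference in the share out of range (intervention minus control, percentage points), with the two percentages where they help:

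| ρ | 60% to 50% | 60% to 40% | 60% to 30% | 40% to 30% |
|---|---|---|---|---|
| −0.3 | −1.1 (14.4 vs 13.3) | −2.3 | −3.5 (14.4 vs 10.9) | −1.2 |
| 0 | 0 | 0 | 0 | 0 |
| 0.1 | +0.5 | +1.0 | +1.5 | +0.6 |
| 0.3 | +1.5 (25.2 vs 26.7) | +3.2 (25.2 vs 28.4) | +5.2 (25.2 vs 30.4) | +2.0 |
| 0.5 | +2.7 | +6.0 | +9.9 (28.5 vs 38.4) | +3.9 |

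On the mean scale, the same scenarios give 0.05 to 0.15 SD at ρ = 0.3 and 0.08 to 0.26 SD at ρ = 0.5.

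**Second model.** A simulation let a latent severity drive both transport (correlation 0.8) and the reading (0.2 to 0.5). The shift toward worse readings was 0.03 to 0.07 SD when transport fell from 50% to 40%, and 0.08 to 0.21 SD from 60% to 30%. It was 0 when both phases transported 40%.

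**Using the pair of readings.** For the change from participating hospital (correlation ρ₁) to perinatal center (ρ₂), the bias is (ρ₂ − ρ₁) times the difference in φ(z)/p, in SDs of a single reading. It is 0 if ρ₁ = ρ₂. With ρ₁ = 0.3 and ρ₂ = 0.2, it runs from −0.1 × 0.154 = −0.015 to −0.1 × 0.515 = −0.052. With ρ₂ = 0.1, it runs from −0.031 to −0.103. In these scenarios pairing reduces the bias but does not always remove it.

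**The case against.** The strongest reply is that the article never states a phase comparison for this row. In Data analysis, the confirmatory models cover the primary outcomes only. The sentence on comparing groups refers to a hypothesis 1 that may be the secondary hypothesis on satisfaction and symptoms, and the abstract also mentions descriptive analyses. This stands in part: the comparison is implied, not spelled out. But a secondary outcome filed under care close to home, the subject of a hypothesis worded against routine care, will naturally be read as compared by phase.

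A second reply is that the row is openly about transport, and that transport quality can only be measured in transported newborns. That is right, and it is a reason to keep the measure. It does not make a phase difference in it an intervention effect.

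A third is that Table 1 already holds the transport counts, the proportion transferred, the paired readings and a 24-hour hypoglycemia outcome. That is also true, and it makes the remedy cheap. But the counts only show that the group changed in size; they do not correct the comparison.

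A fourth is that the bias would be lost in noise. Detecting 25.2% versus 28.4% with 80% power at two-sided 5% takes (1.96 + 0.84)² × (0.252 × 0.748 + 0.284 × 0.716)/0.032², about 3,000 transported newborns per phase without clustering. The whole trial plans 1,417 + 1,541 = 2,958 participants over five bundles. Even 28.5% versus 38.4% takes about 350 per phase. So a falsely significant result from this source is unlikely in the moderate scenarios. The point estimate would still be shifted, and it could be read as a safety signal.

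**Conclusion.** The concern holds, as a minor point. The row conditions on a post-assignment event that the network aims to change, so a phase difference in it cannot be taken as an effect on newborn condition.

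Neither the direction nor the size of the bias can be fixed from the article. Under the assumptions above, with transport falling by 10 to 30 percentage points, it is 0 if avoided transports are unrelated to severity, 1.5 to 5.2 points at a correlation of 0.3, up to 9.9 points at 0.5, and −1.1 to −3.5 points if the sickest stay local. Confidence is medium, because the comparison is implied and an analysis plan that is not shown may already restrict how the row is read.

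**What to change.** - Keep temperature and glucose in transported newborns as a descriptive measure of transport quality, preferably as the change within each newborn from the participating hospital to the perinatal center.
- Show it beside the proportion of transferred newborns in each phase, and state that it is not interpreted as an intervention effect.
- Base the between-phase conclusion on glucose on the hypoglycemia outcome already in Table 1, taken over all IB#2 newborns.
- Do not replace the row with a composite of being transported and out of range: it falls mechanically when transports fall.

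The cost is a change of wording in the outcome list, using data already planned for the project database. The loss is an intervention-effect estimate for temperature, unless a temperature at a fixed postnatal time is already recorded for every IB#2 newborn.

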### Data analysis

As part of the confirmatory analysis, we examine the effectiveness of the intervention bundles using the IB-specific primary outcomes (Chap. 2). A separate logistic multilevel regression model is estimated for each primary outcome, which contains the intervention status (control or intervention phase) of the respective patient or newborn facility as an explanatory variable. The coefficient of this explanatory variable represents the intervention effect. To account for the clustered structure and the possible correlation of patient outcomes within the institutions, all models contain a random intercept at the institutional level [16]. The estimation results support the respective primary hypothesis if the estimated intervention effect is positive and statistically significant. Significance is tested using a two-tailed test with a significance level of 5%. To control for the inflation of the Type 1 error in our setting where we conduct multiple tests, Holm-Bonfferoni correction is used [17].

For testing of hypothesis 1, we compare data for the control and intervention group by analyzing frequencies and mean values, confidence intervals and conducting adjusted regression models.

The qualitative semi-structured interviews will be audio recorded and transcribed verbatim. The transcripts will be analyzed content-analytical using inductive and deductive coding.

Secondary hypothesis 2 (health economic evaluation) will be assessed by analyzing statutory health insurance routine data for each patient case. For each intervention bundle, we sum up the inpatient costs and costs for transfers of the individual patients, and, if mother and child are insured by AOK Plus, costs associated to their newborns in the context of their birth and costs in the 6 months following birth. In the next step, we compare average costs between the intervention and control phase cases and determine the difference in costs. Additionally, we compare the following aspects between the control and intervention group: patient transfers; length of inpatient stays; risks, complications and expenses during the inpatient stay; and more frequent clinic presentations. Expenses for patients and the medical staff involved will be included in the analysis (Table 1, last line).

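### Length of stay at the Perinatal Center is defined only for newborns admitted there, a group that IB#2 and IB#4 aim to shrink, so it need not track Perinatal Center days

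*Protocol article*

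**What the plan says.** In Table 1 of the protocol article (Care close to home, IB#4 rows) one secondary outcome is "Length of stay of newborns at the Perinatal Center of the University Hospital originating from the participating hospitals". No rule is given for newborns of these hospitals who are never admitted to the Perinatal Center (PC). The next row is "Total duration of inpatient care of newborns from participating hospitals".

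The section on IB#4 states the aim that "transfers from the PC-UKD to the hospitals will be promoted and transfers to the PC-UKD will be reduced". The section on IB#2 sets the goal to "reduce neonatal transports" and says of telemedical support: "In some cases, this may even eliminate the need for a neonatologist to travel to the hospital or to transfer the newborn".

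Eligibility for IB#4 is wider than admission to the PC. It begins with "Premature or sick newborn receiving inpatient care at a participating hospital or the PC-UKD with a suspected need for transfer to the PC-UKD" and goes on to include newborns with an indication for transfer back.

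The Data analysis section says, for hypothesis 1, that "we compare data for the control and intervention group by analyzing frequencies and mean values", with confidence intervals and adjusted regression. It names no summary measure for this row.

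**The concern.** Admission to the PC happens after the hospital's phase has been fixed, and the bundles are designed to change how often it happens. Comparing stay among admitted newborns between phases therefore conditions on an event that the intervention affects. Randomising the order in which hospitals switch does not make the two admitted groups comparable.

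A newborn who is managed locally because of the bundle is a success for care close to home. In this row that newborn does not count as zero PC days but disappears. Of the two IB#4 aims, earlier transfer back shortens the measured stays, while fewer transfers in changes whose stays are measured. The row cannot separate the two effects. At stake is whether a secondary outcome in the care-close-to-home group can be interpreted.

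**Working it through.** **Inputs.** The article gives no expected stay, transfer rate or target for this outcome, so there is no stated figure to reproduce. All inputs below are assumptions chosen to show the mechanism.

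Per phase, 200 newborns are eligible. In the control phase 40 have a short PC stay of 5 days, 60 have a long stay of 30 days, and 100 are never admitted.

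**Formulas.** Mean among admitted = PC days / admitted newborns. Mean per eligible newborn = PC days / 200.

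**Control.** PC days = 40×5 + 60×30 = 2,000. Mean among admitted = 2,000/100 = 20.0. Mean per eligible newborn = 2,000/200 = 10.0.

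**Intervention, by which transfers are avoided (other stays unchanged).**

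| Transfers avoided | Admitted | PC days | Mean among admitted | Mean per eligible |
|---|---|---|---|---|
| 25% of short stays | 90 | 1,950 | 21.7 | 9.75 |
| 50% of short stays | 80 | 1,900 | 23.8 | 9.5 |
| 75% of short stays | 70 | 1,850 | 26.4 | 9.25 |
| 50%, unrelated to stay | 50 | 1,000 | 20.0 | 5.0 |
| 25% of long stays | 85 | 1,550 | 18.2 | 7.75 |
| 50% of long stays | 70 | 1,100 | 15.7 | 5.5 |

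PC days fall in all six rows. The mean among admitted rises in three, is unchanged in one and falls in two.

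**Adding earlier transfer back.** Suppose 50% of short-stay transfers are avoided and long stays are 2 days shorter. PC days = 20×5 + 60×28 = 1,780. The mean among admitted is 1,780/80 = 22.25, up 2.25, while the mean per eligible newborn is 1,780/200 = 8.9, down 1.1. The rise vanishes when long stays shorten by x days with 100 + 60(30 − x) = 20×80, so x = 5.0. For 25% and 75% avoidance the break-even is 2.5 and 7.5 days.

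**A second assumed case mix.** Of 100 newborns, 60 are transferred in control, 30 for 5 days and 30 for 25 days. The mean is (30×5 + 30×25)/60 = 15.0 and the total 900 days. Avoiding 25%, 50% or 75% of the short-stay transfers gives 862.5/52.5 = 16.4, 825/45 = 18.3 or 787.5/37.5 = 21.0 days, while the total falls by 4.2%, 8.3% or 12.5%. If every stay is also 10% shorter, 50% avoidance gives 742.5/45 = 16.5 days, with the total down 17.5%.

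**Is days per eligible newborn safe as a replacement?** Not on its own. A suspected need for transfer is a clinical judgement, and the Assignment of interventions section states that there is no blinding. If easier teleconsultation raised the number identified from 200 to 260 with 2,000 PC days unchanged, days per identified newborn would fall from 10.0 to 2,000/260 = 7.7 with nothing saved. Total days per hospital-month would not move.

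**The case against.** The row names a variable, not an analysis. That it will be averaged is inferred: the sentence on mean values is tied to hypothesis 1, and the choice of summary may properly sit in an analysis plan that is not shown. This stands as far as the summary goes. It does not reach the population, because a stay at the PC is undefined for a newborn never admitted there, and a median among the admitted would carry the same selection.

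Table 1 also measures transfers directly. IB#2 has the number of postnatal transports and "Proportion of transferred newborns", and the Economic impact rows for IB#2–5 include the child's number of transfers around the birth stay. A reader who sees fewer transfers beside a longer stay has a warning. This also stands, and it lowers the risk of misreading. But these rows are not combined with stay, total inpatient duration does not separate PC days from days close to home, and no listed outcome gives PC days without conditioning on admission.

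Stay among treated newborns does describe the transfer-back aim. That is a reason to keep it as a description, not to compare it between phases as an effect.

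A reader might infer that the mean stay will rise and make a working bundle look like a failure. The documents do not support that. A rise needs the avoided transfers to be mainly shorter stays and earlier transfer back not to offset them. Local management of milder cases makes the first condition plausible, but nothing in the article documents it.

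**Conclusion.** The point holds in a limited form. As defined, the outcome compares differently selected newborns between phases, and a summary of stay among the admitted can rise, stay unchanged or fall while PC days fall. The documents settle neither direction nor size. The figures above show only that the summary and the days can diverge, under assumed stays, transfer rates and avoidance patterns.

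The outcome is secondary. The confirmatory analysis uses the primary outcomes, and no sample size or success rule is stated for this row, so the trial's main conclusions are not affected. The change is worth making because it is cheap and no other listed row supplies the missing quantity.

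**What to change.** 1. For the comparison between phases, use the total PC days of newborns from each participating hospital per hospital-month, by phase of the originating hospital. Include newborns enrolled while already at the PC-UKD; counting only those enrolled at the hospitals would drop part of the transfer-back group.
2. As a supplement, report PC days per IB#4 newborn from that hospital, with 0 if never admitted, together with the number of IB#4 newborns identified in each phase. That number shows whether the threshold for suspecting a need for transfer has shifted.
3. Keep length of stay among admitted newborns as a descriptive figure, beside the number and proportion transferred.

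The cost is one changed outcome definition, using the data sources already listed for the row (project database and SHI routine data). Day counts are skewed with many zeros, so the interval needs a bootstrap or a count or two-part model. With eight hospitals, precision will be limited.
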